### Provisions for post-trial care {30}

We do not expect participants to suffer harm from trial participation. The two most likely risks associated with this study include potential embarrassment, distress, or anxiety related to discussing difficult financial issues and the possible breach of confidentiality. Risk of distress or anxiety associated with financial costs of care will be directly targeted (and most likely reduced) by the intervention itself, but we acknowledge that exploring the nature of financial distress may be associated with a temporary increase in distress. We expect that both of these risks will be minimized by the careful selection and rigorous training of financial navigators (which will include an emphasis on sensitivity, privacy concerns, confidentiality, ethical behavior, maintaining dignity and respect, and creating a culturally open and non-judgmental environment in which participants feel safe from identification and free to share without harm).

### Outcomes {12}

Outcomes measured in this trial include implementation determinants, implementation outcomes, and patient outcomes (Table 2).

**Table 2 Tab2:** Implementation determinants, implementation outcomes, and patient outcomes assessed in LIFT

Implementation and patient outcome measures	Data source/measurement description	Pre-FN intervention	Post-FN intervention
**Implementation determinants**			
***Financial navigator characteristics***	Financial navigator questionnaire (study-specific instrument) regarding knowledge, self-efficacy and confidence related to FT and FN	X	X
***Intervention*** complexity	Financial navigator and practice stakeholder structured interviews		X
***Outer setting*** patient needs and resources	Financial navigator and practice stakeholder structured interviews		X
***Inner setting*** implementation climate, learning climate, resources and access to information	Financial navigator and practice stakeholder structured interviews		X
***Process*** of reflecting and evaluating	Financial navigator and practice stakeholder structured interviews		X
**Implementation outcomes**			
***Fidelity*** to financial navigation protocol	Assessed via 10% random sample of all FN intake forms and appointment notes recorded by financial navigators in a patient tracking database built in RedCap to assess: whether the full comprehensive intake form was completed, whether participants received at least two visits with the financial navigator, whether the financial navigator re-contacted participants within 2–3 weeks after each financial clinic visit, and level of completeness of tracking data (e.g., were financial assistance applications submitted, was the resolution status recorded?)		X
***Uptake*** of financial navigation intervention	Assessed using patient tracking database in RedCap as the ratio of the number of patients served by FN to the number of patients screened positive for financial distress and referred to FN; and the percentage of patients who are successfully navigated to specific financial assistance resources (including, but not limited to, Social Security Disability Insurance (SSDI); Medicaid; private insurance subsidies; charity care)		X
***Acceptability*** of financial navigation to practices	Financial navigator and practice stakeholder structured interviews		X
Perceived ***sustainability*** of financial navigation	Financial navigator and practice stakeholder structured interviews		X
***Cost*** of financial navigation	Assessed using patient tracking database in RedCap and navigator time-audits as the sum of all wages associated with intervention-related navigator activity for the duration of the study period, specifically: time spent training, time spent with patients delivering financial navigation services, time spent conducting administrative functions (e.g., patient scheduling and tracking, researching financial assistance resources, and submitting and resolving financial assistance applications), and time spent engaged in technical support and tailored coaching		X
**Patient outcomes**			
Socio-demographic variables	Patient survey of age, race, ethnicity, marital status, education, income, employment status, health insurance, household size, and dependents	X	
Cancer-related financial toxicity	COmprehensive Score for financial Toxicity (COST) instrument	X	X
Emotional distress and anxiety	PROMIS Emotional Distress-Anxiety Short Form 6a: 6-item measure of anxiety over the past 7 days	X	X
Depression	PROMIS Depression Short Form 8a: 8-item measure of depression over the past 7 days	X	X
Health-related quality of life	PROMIS Global Health Questionnaire: 10-item measure of symptoms, functioning, and healthcare-related quality of life (HRQoL)	X	X
Illness impact	Psychosocial Illness Impact Short Form-Pos 4a: 4-item measure of positive emotional and social outcomes of illness	X	X
Care-altering behaviors (foregoing, delaying care)	Patient questionnaire (study-specific instrument)	X	X
Patient perspectives on FN acceptability, responsiveness and alignment with needs, patient-centeredness, and timeliness	Patient questionnaire (study-specific instrument)		X

#### Implementation determinants

Determinants of implementation success (or failure) will be evaluated using CFIR and include, briefly: intervention complexity; outer setting patient needs and resources; inner setting implementation climate, learning climate, resources and access to information; individual characteristics of knowledge, self-efficacy and confidence, and the process of reflecting and evaluating [29]. Implementation determinants will be assessed through in-depth, structured post-implementation interviews with financial navigators and other key practice-level stakeholders. A draft semi-structured interview guide is included in Additional file 1.

#### Implementation outcomes

The quality of implementation assessment will be guided by Proctor and colleagues’ implementation outcomes framework and include analysis of fidelity, uptake, acceptability, costs, and perceived sustainability [30]. Intervention acceptability and perceived sustainability will be assessed through in-depth, structured post-implementation interviews. We will measure fidelity by reviewing a 10% random sample of all FN intake forms and appointment notes recorded by financial navigators in a participant tracking database built in REDCap to assess: whether the full comprehensive intake form was completed, whether participants received at least two visits with the financial navigator, whether the financial navigator re-contacted participants within 2-3 weeks after each financial clinic visit, and level of completeness of tracking data (e.g., were financial assistance applications submitted, and was the resolution status recorded). Uptake will be assessed as the ratio of the number of participants served by FN to the number of patients screened positive for financial distress and referred to FN, and the percentage of participants who are successfully navigated to specific financial aid resources. Costs will be measured on a per-practice level as the sum of all wages associated with intervention-related navigator activity for the duration of the study period, specifically: time spent training, time spent with participants delivering financial navigation services, time spent conducting administrative functions (e.g., participant scheduling and tracking, researching financial assistance resources, and submitting and resolving financial assistance applications), and time spent engaged in technical assistance and peer support calls. These cost data will be captured through activities recorded in the participant tracking database and random navigator weekly time-audits.

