### Trial design {8}

This is a prospective, multi-site, non-randomized Phase 2 clinical trial of a behavioral intervention targeting individual patients. We will use a pre- and post-FN single-arm intervention approach following a “Type II” implementation-effectiveness hybrid design with equal weight given to implementation and effectiveness outcomes. We acknowledge that a randomized, controlled design may be preferred from a statistical perspective; however, none of the participating oncology practices were interested in being randomized to a control arm, and withholding FN may have been perceived as unethical in this context; therefore, a pre-/post-FN, single-arm design was chosen.

A conceptual framework of financial burden following cancer diagnosis developed by Jones and colleagues guided the trial design and selection of outcomes [24]. In this framework, costs associated with cancer diagnosis and treatment, moderated by pre-cancer health and socioeconomic status, lead to overall financial burden, comprised of psychological (i.e., worry, ruminations) and material components (e.g., care-altering behaviors). The result of this overall financial burden, within the context of healthcare system practices (such as financial navigation), translates into patient outcomes (e.g., health-related quality of life, anxiety, and depression) [24].

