### Sample size {14}

We anticipate enrolling a total of 780 participants into the study in order to include 700 participants in the final analysis, allowing for attrition of up to 10%. We aim to include approximately 100 participants in the final analysis per rural site and 50 participants per non-rural site. We considered a very conservative pre/post-FN intervention effect (difference in COST scores) as small as 0.5 as well as a more considerable intervention effect as large as 3.0. A one-sample paired t-test (pre-/post- analysis of the change in COST FT score) with alpha=.05, will have 80% power to detect an effect size of 0.106. This may be seen with an average difference of 1 point, and a standard deviation of 9.43, or a mean difference of 3 points, and a standard deviation of 28.29. Notably, the UNC pilot project on which this study is based found a nearly 7-point improvement in COST FT score post-FN intervention completion.

Given our 2% (1/50) attrition rate for the UNC pilot project this study is based on [32], we do not expect much attrition. If participants are lost to follow-up between consent and their first FN visit, we will replace them since they did not receive the intervention.

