### Data management {19}

All participant data will be collected and managed via each site’s individual REDCap database, including all baseline surveys, intake forms, check-in forms, and end of study surveys. Medical record data will be abstracted by the trained financial navigator from the site’s electronic medical record and entered into REDCap as needed, such as treatment status and appointment information.

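### Fidelity rests on a 10% sample of forms and notes although all forms are in REDCap: this is thin for the rural versus non-rural comparison and favours participants with more visits

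*Protocol article*

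**What the plan says.** Under Outcomes {12}, Implementation outcomes, the article says: "We will measure fidelity by reviewing a 10% random sample of all FN intake forms and appointment notes recorded by financial navigators". Table 2 repeats the 10% fraction and the same unit. Four things are checked. Two concern the records themselves: completion of the intake form and completeness of the tracking data. Two concern a participant's contacts. One of these is "whether participants received at least two visits with the financial navigator". The other is a timing check on follow-up: "whether the financial navigator re-contacted participants within 2-3 weeks after each financial clinic visit".

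Data management {19} places all participant data in REDCap, "including all baseline surveys, intake forms, check-in forms, and end of study surveys". Plans for assessment and collection of outcomes {18a} requires an intake form at the first appointment and a check-in form at each later one. For uptake, Table 2 names the same tracking database as the source and states no sampling.

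Trial design {8} describes a hybrid design with "equal weight given to implementation and effectiveness outcomes". Objectives {7} lists fidelity among the implementation outcomes and asks for these outcomes in both rural and non-rural settings. The statistical methods section {20a} plans a descriptive checklist for fidelity, with no test, threshold or precision target.

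**The concern.** Two choices are fixed in the text, and each has a cost.

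- **The fraction.** Some of the fidelity items look countable from forms already stored for everyone. Scoring them on one participant in ten adds sampling error that could be avoided. The loss is greatest in the smaller, non-rural group.
- **The unit.** The draw is worded as one of forms and notes, but two of the four criteria describe a participant's whole series of contacts. If records are drawn, a participant with many visits is more likely to be reached than one who came once.

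In a single-arm study whose intervention intensity varies by patient, fidelity is part of how the effectiveness result will be interpreted. An imprecise or flattering figure could mislead about delivery in the two settings.

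**Working it through.** **Inputs.** Sample size {14}: "We anticipate enrolling a total of 780 participants into the study in order to include 700 participants in the final analysis"; "We aim to include approximately 100 participants in the final analysis per rural site and 50 participants per non-rural site"; attrition allowance 10%. Study setting {9}: five rural and four non-rural sites. Participant timeline {13}: at least two visits each. The 80% fidelity used below is an assumption for illustration; the article gives no expected value.

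**The plan's own figures.** 5 × 100 + 4 × 50 = 700 analysed. 700 / 0.9 = 778, against 780 stated. Both reproduce. The article gives no count of fidelity records.

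**Size of the 10% sample, counted as participants.**
- Analysed: 70 overall, 50 rural, 20 non-rural.
- Enrolled: 500 / 0.9 = 556 rural and 200 / 0.9 = 222 non-rural, so about 56 and 22 sampled (78 in all).
- Per non-rural site: 10% of 50 = 5.

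Counted instead as forms and notes, a 50-participant site holds at least 50 × 2 = 100 records, so at least about 10 are sampled.

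**Precision at 80% fidelity** (95% half-width; 0.8 × 0.2 = 0.16).

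| Quantity | Formula | Half-width |
|---|---|---|
| Pooled, 78 | 1.96 × √(0.16/78) | 8.9 points |
| Pooled, 70 | 1.96 × √(0.16/70) | 9.4 points |
| Rural − non-rural, 56 vs 22 | 1.96 × √(0.16/56 + 0.16/22) | 19.7 points |
| Rural − non-rural, 50 vs 20 | 1.96 × √(0.16/50 + 0.16/20) | 20.7 points |
| Rural − non-rural, all enrolled, 556 vs 222 | 1.96 × √(0.16/556 + 0.16/222) | 6.2 points |
| Rural − non-rural, all analysed, 500 vs 200 | 1.96 × √(0.16/500 + 0.16/200) | 6.6 points |

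Exact 95% intervals: 16 of 20 (non-rural group) gives 56% to 94%; 40 of 50 (rural group) gives 66% to 90%; 4 of 5 (one non-rural site) gives 28% to 99%.

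These figures treat the participants as a sample from a wider population. If the aim is only to describe those enrolled, the 10% half-widths shrink by √0.9 = 0.949, so 19.7 becomes 18.7 points. Scoring everyone then leaves no sampling error at all.

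**Selection by record.** Suppose (assumed) 80% of participants have three records each and 20% have one. Per participant, records from those with at least two visits average 0.8 × 3 = 2.4, and the others contribute 0.2 × 1 = 0.2. A record drawn at random belongs to a participant who meets the criterion with probability 2.4 / 2.6 = 92%, against a true 80%. With one record per visit, the direction is fixed for the two-visit criterion. For re-contact it is less certain: later visits are themselves evidence of contact, but more visits also mean more intervals that must all be met.

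**The case against.** The strongest reply has four parts.

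1. **Only description is planned.** There is no per-site fidelity estimate, threshold or test, and about 9 points pooled is enough to describe. This stands for the pooled figure. It does not answer the setting-level objective.
2. **The criteria can still be scored.** A reader might infer that sampling forms and notes makes the participant-level criteria impossible to assess. The article does not support that. A check-in form itself shows a second visit, a reviewer can open the participant's other entries, and the wording can be read as a review of participants' files. What remains is an unclear unit and, if records are drawn, unequal chances of selection. Opening the rest of the file does not remove the latter.
3. **Not every item is known to be a field.** The text speaks of appointment notes, re-contact may be by visit, text, phone or email, and the form layouts are in additional files not shown. This stands: the article does not show that all four items can be queried, and sampling is reasonable where notes must be read.
4. **Silence on stratification is not a decision against it.** A condensed article may leave this to the full protocol, and separate site databases are compatible with drawing by site. This also stands. A reader might also take the sample to be about five records per non-rural site; five is a count of participants, and in forms and notes the figure is at least about 10.

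**Conclusion.** The point holds in a limited form. The 10% fraction and the form-and-note unit are stated choices, and no reason is given for applying them to items that could be counted on everyone. At an assumed 80% fidelity and the planned site sizes, the cost is a half-width of about 20 points instead of about 6 for the setting difference, and an interval of 56% to 94% for the non-rural group. If records are the unit, the two-visit criterion can also be overstated; the rise from 80% to 92% is an illustration that depends on the assumed visit pattern. The stronger conclusion, that the sample cannot describe fidelity at all, is not supported, because pooled precision is acceptable. No primary or secondary patient-outcome analysis is affected.

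**What to change.** - Compute the items stored as form completion, visit counts, dates or status fields on 100% of participants, with the participant as the unit, and report them by rural and non-rural setting.
- Keep the 10% manual review only for items that need notes to be read. Sample participants within site, and review all records of each sampled participant.
- State in the protocol which items fall under each route.

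The cost is a small programming task and a short change of text, with no new data collection. Any item not held as a structured field stays in the manual sample, with the precision shown above.

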#### Patient Outcomes

The primary patient outcome will be change in FT from baseline to follow-up, as measured by pre-/post-intervention completion of the Comprehensive Score for Financial Toxicity (COST) tool. The COST score was selected as the primary outcome given that it has been validated in adult patients with cancer and has been shown to be associated with relevant clinical outcomes (e.g., health-related quality of life) [27]. We will assess mean pre-/post-FN intervention COST scores, which range from 0-44 with a population mean of 22.

Secondary outcomes will include change in HRQoL and change in care-altering behavior. HRQoL will be measured using the PROMIS Global Health Questionnaire, which is a 10-item measure of symptoms, functioning, and HRQoL. We selected this secondary outcome due to the documented negative association between financial burden and HRQoL in the literature [8, 9]. We will assess differences in mean pre-/post-FN intervention HRQoL scores.

Change in care-altering behavior will be operationalized as a dichotomous outcome of forgoing or delaying care due to cost. Harmful, care-altering behavioral responses to the high cost of care, including discontinuation of and non-adherence to medications and delaying or foregoing medical treatment, may contribute to widely observed disparities in cancer mortality by rurality and socioeconomic status [1, 9, 23, 31]. We will assess mean pre-/post-FN intervention differences in the probability of forgoing or delaying care.

Additional patient outcomes will include anxiety, depression, and psychosocial illness impact, all measured using validated PROMIS scales. We will also describe frequencies, proportions, means and standard deviations, as appropriate, of patient-reported post-FN intervention convenience, accessibility, satisfaction, responsiveness (alignment with needs), patient-centeredness, and timeliness. We will use a study-specific patient questionnaire to assess these descriptive outcomes.

### Participant timeline {13}

Following informed consent and baseline survey completion, participants referred to a financial navigator will have at least 2 visits (intake, follow-up), 2–3 weeks apart, with the navigator, with some participants receiving more intensive, needs-dependent support. The anticipated duration of the program for participants will be between 2 weeks and 6 months, depending on needs. Participants will be asked to complete a follow-up survey 2–3 months after intervention completion to allow time for FN to have an effect on outcomes. A schematic diagram of participant enrollment, intervention, and assessments is shown in Figs. 1 and 2 shows an accompanying flowchart of the intervention.

**Fig. 1 Fig1:**
[figure not shown]
LIFT participant timeline of enrollment, intervention, and assessments. *Timing and number of follow-up visits will vary depending on each patient’s needs. ** Patient questionnaire (study-specific instrument) on FN acceptability, responsiveness and alignment with needs, patient-centeredness, and timeliness

**Fig. 2 Fig2:**
[figure not shown]
LIFT intervention flow chart

### Sample size {14}

We anticipate enrolling a total of 780 participants into the study in order to include 700 participants in the final analysis, allowing for attrition of up to 10%. We aim to include approximately 100 participants in the final analysis per rural site and 50 participants per non-rural site. We considered a very conservative pre/post-FN intervention effect (difference in COST scores) as small as 0.5 as well as a more considerable intervention effect as large as 3.0. A one-sample paired t-test (pre-/post- analysis of the change in COST FT score) with alpha=.05, will have 80% power to detect an effect size of 0.106. This may be seen with an average difference of 1 point, and a standard deviation of 9.43, or a mean difference of 3 points, and a standard deviation of 28.29. Notably, the UNC pilot project on which this study is based found a nearly 7-point improvement in COST FT score post-FN intervention completion.

Given our 2% (1/50) attrition rate for the UNC pilot project this study is based on [32], we do not expect much attrition. If participants are lost to follow-up between consent and their first FN visit, we will replace them since they did not receive the intervention.

### Recruitment {15}

Patients will be identified by the site staff as potentially eligible for this study based on the study eligibility criteria detailed above, and all eligibility criteria will be verified after approaching patients. Sample recruitment materials are included in Additional file 2. Recruitment of patients will be subject to established protocols defined by UNC and participating institutions. Patients will be recruited by site staff during routine clinic visits to a participating site; therefore, recruitment will not require outreach to patients who are not receiving care currently in the partner oncology sites. Each site will use a combination of passive recruitment (flyers) and active recruitment (staff introduction of the study to the patient if the patient expresses financial concerns). In most cases, staff introducing the study will be financial navigators or social workers. In both active and passive recruitment activities, it will be clear that a patient’s decision regarding participation in the study will not influence the care that they receive. In our pilot study, we were able to recruit 50 participants in four months [32]. As such, we do not anticipate challenges recruiting enough eligible participants to reach the target sample size at each site.

